### Sample size

In a pilot study the 2 weeks headache diary showed an average of 11 days with headache in both treatment groups at baseline. After 8 weeks the frequency of days with headache in the GP group was reduced to 7 days, in the MT group to 3 days. In the full trial we aim to detect a difference in reduction of at least 3 days (SD 5) between both groups. To detect this difference with a one-sided significance level of 0.05, and power of 0.80 we have to include at least 35 patients in each treatment group. The participants in the pilot study reported taking on average 2 doses of NSAID or analgesics per 2 weeks. With a sample size of 35 patients per group we can detect a difference of at least 0.5 (SD 0.8) doses per 2 weeks between the groups. With a calculated loss of participants in the full trial of 15%, this trial attempts to enroll forty-two patients with CTTH in each treatment groups (GP, MT).

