### Statistical analysis

Baseline comparability will be investigated by descriptive statistics to examine whether randomisation was successful. For each patient, the change between baseline and follow-up will be calculated for all primary and secondary outcome measures. The statistical analysis will be performed according to the intention-to-treat principle.

Between group differences and 95% confidence intervals will be calculated, and tested using the Student t-test in case of normal distributions. Non paramaratric testing will be used for non-normal distributions. In addition, a per-protocol analysis will be performed, analysing only those patients with no serious protocol deviations. Comparing the results of the intention-to-treat and the per-protocol analysis will indicate if and to what extent protocol deviations might have influenced the results. Multivariate regression analysis will be conducted to examine the potential influence of differences in baseline characteristics on outcome.

If results on primary outcomes show normal distributions we will compute effect sizes (standardised mean differences) as the mean difference between groups over the pooled standard deviation. Effect sizes will be rates as follows: small (0.2–0.5), medium (0.5–0.8) or large (>0.8).

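### The 80% power holds for a one-sided 5% test, but under the 95% confidence intervals the analysis reports, 35 patients per arm give about 70% power

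*Protocol article*

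**What the plan says.** The Sample size section of the protocol article sets the target for headache days: "we aim to detect a difference in reduction of at least 3 days (SD 5) between both groups". It then derives the number of patients: "with a one-sided significance level of 0.05, and power of 0.80 we have to include at least 35 patients" per arm. For the other primary outcome, medication use, it adds: "With a sample size of 35 patients per group we can detect a difference of at least 0.5 (SD 0.8) doses per 2 weeks". That sentence gives no significance level or power of its own. Allowance for loss follows: "With a calculated loss of participants in the full trial of 15%, this trial attempts to enroll forty-two patients with CTTH in each treatment groups".

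The Statistical analysis section describes the comparison: "Between group differences and 95% confidence intervals will be calculated, and tested using the Student t-test in case of normal distributions". It does not say whether the test is one-sided or two-sided, and it mentions neither a one-sided confidence bound nor a 90% interval. No other section gives a reason for the one-sided level.

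**The concern.** A 95% confidence interval for a difference, without further qualification, is two-sided. It excludes zero exactly when the two-sided t-test has p below 0.05, that is, when the one-sided p in the observed direction is below 0.025. The sample size rests on a one-sided p below 0.05. A result for manual therapy with a one-sided p between 0.025 and 0.05 would therefore count as significant by the standard used for sizing, while its reported interval included zero. The article does not say which governs.

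Two things are at stake. First, the stated 80% power does not apply to the intervals that readers will see. Second, a one-sided 5% rule doubles the conventional 2.5% false-positive risk in favour of manual therapy. That matters here because patients, GPs and therapists are not blinded, both primary outcomes come from patient diaries, and the Discussion reports that most pilot patients preferred manual therapy.

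One-sidedness also sits poorly with the purpose. The Discussion presents both arms as forms of usual care and wants the result to guide GPs on referral. A finding that GP care does better would bear on that decision too.

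**Working it through.** **Inputs, all from the Sample size section.** Headache days: difference 3, SD 5, so d = 3/5 = 0.6. Medication: difference 0.5, SD 0.8, so d = 0.5/0.8 = 0.625. Evaluable patients 35 per arm, 1:1. Level 0.05 one-sided, power 0.80. Loss 15%.

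**Reproducing the plan's figure.** With the normal approximation, n per arm = 2(z_α + z_β)²(SD/difference)².
- One-sided 5%: 2 × (1.645 + 0.842)² × (5/3)² = 34.35, rounded up to 35. The exact t-test solution is 35.04.
- Loss: 35/0.85 = 41.2, rounded up to 42.

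Both stated numbers reproduce.

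**The same formula at two-sided 5%.** 2 × (1.960 + 0.842)² × (5/3)² = 43.60, rounded up to 44. The exact t-test solution is 44.59, rounded up to 45. After 15% loss this means 44/0.85 = 51.8, so 52, or 45/0.85 = 52.9, so 53 enrolled per arm.

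**Power at the planned size.** The standard error of the headache-day difference is 5 × √(2/35) = 1.195 days, and 3/1.195 = 2.510.
- Normal approximation: one-sided Φ(2.510 − 1.645) = 80.7%; two-sided Φ(2.510 − 1.960) = 70.9%.
- The planned t-test (noncentral t, 68 degrees of freedom) gives:

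| Outcome | Analysed per arm | One-sided 5% | Two-sided 5% |
|---|---|---|---|
| Headache days, d = 0.6 | 35 | 80.0% | 69.7% |
| Headache days, d = 0.6 | 42 (no loss; 82 df) | 86.0% | 77.6% |
| Medication, d = 0.625 | 35 | 82.7% | 73.2% |
| Medication, d = 0.625 | 42 (no loss; 82 df) | 88.4% | 80.8% |

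**Detectable difference at 35 per arm, two-sided 5%, 80% power.** Normal approximation: (1.960 + 0.842) × 1.195 = 3.35 days. With the t distribution it is 3.40 days.

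**Where the two standards disagree.** At 35 per arm with an observed SD of 5, the one-sided 5% test is met at 1.668 × 1.195 = 1.99 days. The 95% interval excludes zero only from 1.995 × 1.195 = 2.39 days (to rounding). An observed advantage for manual therapy between 1.99 and 2.39 days would pass the first standard and fail the second.

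**The case against.** The strongest reply is that nothing is miscalculated. The section states its level, sidedness, difference, SD and power, and 35 per arm follows. That is right, and the 80% is true on those terms. The fault is one of alignment between sample size and analysis.

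A second reply is that the Statistical analysis section never calls its intervals two-sided and never says that significance is read from whether they exclude zero. A one-sided test may stand beside a 95% interval given for estimation, and an analysis plan not shown may settle the sidedness. The two-sided reading is indeed an inference, though the conventional one. But neither choice in a later plan removes the problem. If the tests are two-sided, the stated power is too high for them. If they are one-sided at 5%, the intervals do not match the decision rule.

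Third, the article leans in one direction: it hypothesises that manual therapy helps, and for a referral decision no difference and GP care being better may lead to the same action. This is arguable, and a one-sided test is not wrong in principle. It would still need a stated reason and a matching interval.

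Fourth, the practical loss may be smaller than 70% suggests. The pilot difference after 8 weeks was 7 − 3 = 4 days. At 4 days and SD 5, two-sided power with 35 per arm is about 91%, and medication reaches 80.8% if all 42 per arm are analysed. Both figures are correct. However, the trial's declared target is 3 days with 35 evaluable patients per arm, so about 70% is the figure that corresponds to the plan.

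**Conclusion.** The concern holds. The sample size and the reported intervals use different error standards, and the article neither justifies nor reconciles them. Under the two-sided 5% standard implied by 95% intervals, power at 35 completers per arm is 69.7% for headache days and 73.2% for medication, about 10 percentage points below the one-sided figures (80.0% and 82.7%). For headache days, even full retention of 42 per arm gives only 77.6%.

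This rests on the conventional two-sided reading of the intervals, the stated differences and SDs, a t-test on change scores, and, for medication, the same 5% level as for headache days. The estimate and its interval are unaffected. What changes is the threshold for claiming an effect and the power that readers are told the trial has.

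**What to change.** Before any outcome data are seen:

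- State in the Statistical analysis section that all between-group tests are two-sided at 5%, matching the 95% intervals.
- In the Sample size section, restate power at 35 completers per arm as about 70% for 3 headache days and about 73% for 0.5 doses. Alternatively, give the headache-day difference detectable with 80% power, about 3.4 days.

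Adjusting the comparison for the baseline value may recover part of the lost power. How much depends on the correlation between baseline and follow-up, which the article does not give, so no gain should be claimed in the restated figures.

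The cost is a short wording change and a less favourable stated power. No additional patients, measurements or visits are required.

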### Study population

Participating primary healthcare centers and GPs in an urban area in the Netherlands, will invite patients with headache to participate in the trial.

Patients between 18 and 65 years of age are invited if they have CTTH according to the classification of headaches of the IHS [22]: headache occuring on at least 15 days on average per month for a period of more than 3 months (≥ 180 days a year) and lasts for hours or may be continuous. The headache has at least one of the following characteristics: 1. bilateral location, 2. pressing/tightening (non pulsating) quality, 3. mild or moderate intensity, not aggravated by normal physical activities such as walking or climbing stairs; and both of the following: 1. no more than one of photofobia, phonophobia or mild nausea, and 2. neither moderate or severe nausea nor vomiting. Participants should be able to read and write Dutch.

Exclusion criteria include reumatoid arthritis, suspected malignancy, pregnancy, intake of either triptans, ergotamines or opioids on ≥ 10 days/month or simple analgesics on ≥ 15 days/month on a regular basis for ≥ 3 months, and having received manual therapy treatment in the 2 months before enrolment into the study.

After the GP has seen a patient with CTTH the patient receives an information letter about the trial. If the patient is willing to participate after reading the information he or she can contact the research centre. A researcher will screen interested patients by telephone and make an appointment to check inclusion and exclusion criteria, and complete the informed consent procedure. After written informed consent has been obtained, the baseline measurement is carried out. The design of the trial is explained in Figure 1.

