### Primary outcome measures

The follow-up measurements will take place by a blinded research assistant immediately after the 8 weeks treatment period and after 26 weeks (long term follow-up). Two weeks before each measurement the patients receive and complete a two-week headache diary. The primary outcome measures are 1) the frequency of days with headache, and 2) use of pain medication (no. of doses NSAIDs or simple analgesics). Registration over a two week period is considered to be sufficient.[24]

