### Feasibility of the study design

A pilot study was conduced between June 2006 and December 2006 to evaluate the feasibility of the measurements, randomisation-procedure and treatment protocols (33). The recruitment of participants for this pilot-study took place in two primary health-care centers in The Netherlands. A total of 20 patients were randomised to either the GP or the MT intervention group. Thirty-one patients who had a strong preference for the manual therapy intervention and could not be randomised were asked to participate in a parallel cohort-study. In this study similar baseline and follow up measurements were conducted.

The results of the pilot study showed that the procedures were feasible. The research-assistants, general practitioners and manual therapists reported having no problems to adhere to the guidelines and protocols for measurements and treatment. In order to include a total of 80 patients over a period of one year, 32 GPs and 4 MTs have been recruited to participate in the full trial.

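### The SD of 0.8 behind the detectable difference in medication doses has no stated source or scale and is probably optimistic, so the 0.5-dose claim should become a range

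*Protocol article*

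**What the plan says.** The article's Primary outcome measures section names two primary outcomes from a two-week diary: days with headache, and "use of pain medication (no. of doses NSAIDs or simple analgesics").

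The Sample size section sizes the trial on the first: "we aim to detect a difference in reduction of at least 3 days (SD 5) between both groups", "with a one-sided significance level of 0.05, and power of 0.80", giving "we have to include at least 35 patients in each treatment group". It then turns to medication. "The participants in the pilot study reported taking on average 2 doses of NSAID or analgesics per 2 weeks", and at 35 per group "we can detect a difference of at least 0.5 (SD 0.8) doses per 2 weeks between the groups". No pilot SD for doses is reported, and 0.8 is not tied to the pilot or to a particular scale.

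Study population excludes patients who regularly take "simple analgesics on ≥ 15 days/month on a regular basis for ≥ 3 months", and sets no minimum use. Statistical analysis calculates change from baseline for every outcome and compares groups with a t-test, or a non-parametric test if the distribution is not normal.

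**The concern.** Medication use is a primary outcome, and the sentence on it is the only statement of what the trial can show there. It depends entirely on the 0.8. A dose count cannot go below 0 and typically combines patients who take nothing with a few regular users, and the eligibility rules admit both. A spread of only 0.8 around a mean of 2 would require nearly all patients to take between one and three doses.

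If the true SD is larger, the trial could easily miss a 0.5-dose difference. A null result could then be read as evidence against an effect of that size, because the published plan says it is detectable.

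**Working it through.** **Inputs.** From Sample size: 35 per group, one-sided 0.05, power 0.80, difference 0.5, SD 0.8, pilot mean 2. The level and power are stated for headache days; I assume that they carry over to doses. From Study population: no minimum use, and simple analgesics on up to 14 days a month, which is about 7 days per two weeks with no cap on doses per day.

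**1. The plan's own figure.** Detectable difference = (1.645 + 0.842) × SD × √(2/35). At SD 0.8 this is 2.487 × 0.8 × 0.239 = 0.48, so 0.5 is met. Power for 0.5 is 0.834 (0.827 by the noncentral t). The figure reproduces.

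**2. Slack.** By the noncentral t, 80% power at 35 per group needs a standardised difference of 0.600. The largest SD that keeps 80% power for 0.5 doses is therefore 0.5/0.600 = 0.83 (0.84 by the normal approximation).

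**3. If 0.8 is the SD of a single diary.** Two bounds hold for any distribution with mean 2.
- If a fraction p takes no doses, the variance is at least 4p + (1 − p)(2/(1 − p) − 2)² = 4p/(1 − p). Setting this to 0.8² = 0.64 gives p = 0.16/1.16 = 13.8%. With more non-users than that, an SD of 0.8 is impossible.
- If a fraction q takes 7 doses (one on each of 7 days), the variance is at least 25q/(1 − q). Setting this to 0.64 gives q = 0.0256/1.0256 = 2.5%, or 1 patient in 40.

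For reference, a Poisson count with mean 2 has variance 2 and SD 1.41. A variance of 0.64 is 0.64/2 = 32% of that.

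**4. If 0.8 is the SD of the change.** With equal SD s at both times and correlation r, the change SD is s√(2(1 − r)), so r = 1 − 0.64/(2s²). The correlation needed is 0.50 at s = 0.8, 0.68 at s = 1.0, 0.84 at s = 1.41 and 0.92 at s = 2. Correlations as high as the last two mean very stable individual use. The GP intervention section allows pain medication to be prescribed or changed, and the plan gives the reduction in headache days an SD of 5.

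**5. Sensitivity.** Difference 0.5, 35 per group, one-sided 0.05. SDs above 0.8 are assumptions.

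| SD | Power, normal approx. | Power, noncentral t | Difference detectable at 80% (noncentral t) |
|---|---|---|---|
| 0.8 | 0.834 | 0.827 | 0.48 |
| 1.0 | 0.672 | 0.665 | 0.60 |
| 1.41 | 0.436 | 0.430 | 0.85 |
| 2 | 0.275 | 0.271 | 1.20 |

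**6. What baseline adjustment does.** On the same equal-SD assumption, the residual SD with baseline as a linear covariate is s√(1 − r²), against s√(2(1 − r)) for raw change. At s = 1.41 and r = 0.5 these are 1.41 × √0.75 = 1.22 and 1.41 × √1 = 1.41.

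**The case against.** The claim is conditional and correct. The SD is printed beside the difference, so a reader can rescale it, and no figure in the article contradicts 0.8. Eligibility permits a wide spread but does not show one, and the pilot mean of 2 lies well below the ceiling. Poisson spread is my benchmark, not the plan's. Because the analysis is on change, a change-score SD is a natural reading; 0.8 then needs a correlation of only 0.50 if the single-diary SD is also 0.8. A uniform treatment shift would lower neither the correlation nor the precision. The source of 0.8 may be in the full protocol or the pilot report, and the planned 95% confidence intervals would expose an imprecise null result.

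Most of this stands. It rules out two stronger readings that a reader might reach:
- **That the trial will fail to deliver the 0.5-dose sensitivity.** That requires a larger SD, which the article does not report.
- **That 0.8 was chosen to fit, because 0.5/0.8 = 0.63 lies close to 3/5 = 0.60 for headache days.** Any correct calculation at 35 per group with this level and power gives a ratio near 0.60, so the match says nothing about where 0.8 came from.

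What the objection leaves untouched is step 3, which needs no distributional model, and the near-absence of slack in step 2. Confidence intervals help at the reporting stage but do not correct an optimistic statement in the plan.

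**Conclusion.** The point holds as one about an optimistic planning value, not as a demonstrated power failure. The stated figure is arithmetically right at SD 0.8. That SD has no stated source or scale. As a single-diary SD it is impossible if more than about 14% of patients take nothing or more than about 2.5% take 7 doses. As a change SD it needs a correlation of 0.84 at Poisson spread. Power for 0.5 doses falls below 0.80 once the SD passes about 0.83, and to roughly 0.67, 0.43 and 0.27 at SDs of 1.0, 1.41 and 2.

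This rests on the one-sided 0.05 level carrying over to doses, a mean of 2 for the step 3 bounds, equal SDs at both times for the correlations, and SDs above 0.8 being illustrative. Whether a one-sided level is appropriate is a separate question and adds no weight here. The change is worth making because it concerns a stated number for a primary outcome and costs almost nothing.

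**What to change.** 1. Keep the sample size. In Sample size, say whether 0.8 is a single-diary or change SD and where it comes from. Replace the single 0.5-dose claim with the detectable difference over a range of SDs at 35 per group, one-sided 0.05: about 0.48 at 0.8, 0.60 at 1.0, 0.85 at 1.41 and 1.20 at 2. State that the trial is sized on headache days only.
2. In Statistical analysis, make the main comparison of doses baseline-adjusted: follow-up doses as the outcome and baseline doses as a covariate, with a 95% confidence interval. A count model that allows over-dispersion, such as a negative binomial, is one suitable choice. This replaces the t-test or non-parametric test on raw change. The regression already planned for baseline differences does not do this job, because the main comparison remains on change.

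The cost is a less favourable stated figure and slightly more analysis work. No extra patients or data are needed.

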### Statistical analysis

Baseline comparability will be investigated by descriptive statistics to examine whether randomisation was successful. For each patient, the change between baseline and follow-up will be calculated for all primary and secondary outcome measures. The statistical analysis will be performed according to the intention-to-treat principle.

Between group differences and 95% confidence intervals will be calculated, and tested using the Student t-test in case of normal distributions. Non paramaratric testing will be used for non-normal distributions. In addition, a per-protocol analysis will be performed, analysing only those patients with no serious protocol deviations. Comparing the results of the intention-to-treat and the per-protocol analysis will indicate if and to what extent protocol deviations might have influenced the results. Multivariate regression analysis will be conducted to examine the potential influence of differences in baseline characteristics on outcome.

If results on primary outcomes show normal distributions we will compute effect sizes (standardised mean differences) as the mean difference between groups over the pooled standard deviation. Effect sizes will be rates as follows: small (0.2–0.5), medium (0.5–0.8) or large (>0.8).

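### The main comparison is an unadjusted t-test on change scores; pre-specifying the baseline diary value as a covariate costs almost nothing and is never less precise in large samples

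*Protocol article*

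**What the plan says.** The Statistical analysis section defines the quantity to be compared: "For each patient, the change between baseline and follow-up will be calculated for all primary and secondary outcome measures". Group differences with 95% confidence intervals follow, "tested using the Student t-test in case of normal distributions". For other distributions the text says "Non paramaratric testing will be used for non-normal distributions". Baseline information enters a model only in a later sentence: "Multivariate regression analysis will be conducted to examine the potential influence of differences in baseline characteristics on outcome". That sentence follows the per-protocol analysis and names no covariates.

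The Sample size section plans for the same quantity: "we aim to detect a difference in reduction of at least 3 days (SD 5) between both groups", "with a one-sided significance level of 0.05, and power of 0.80 we have to include at least 35 patients in each treatment group". Table 1 lists headache frequency and medication use, both from the diary, at baseline, 8 weeks and 26 weeks. Each primary outcome therefore has a baseline value on the same scale.

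**The concern.** A change score subtracts the whole baseline value, which amounts to fixing the slope of follow-up on baseline at 1. If the true slope is below 1, chance differences at baseline are over-corrected; if it is above 1, they are under-corrected. Either way the comparison carries variance that a model with an estimated slope would remove. A regression that only supports the main result does not help the main estimate or its confidence interval.

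With about 35 patients analysed per arm, a chance imbalance at baseline is to be expected and precision is scarce. The baseline diaries are already being collected, so any precision left unused has been paid for. This is also a choice that the article makes, not a detail that it leaves open: a later analysis plan would have to change it.

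**Working it through.** **1. The plan's own figure.** Inputs from the Sample size section: difference 3 days, SD 5, one-sided 0.05, power 0.80. The normal formula gives n = 2 × (1.645 + 0.842)² × 5² / 3² = 34.4, so 35 per arm. Allowing for 15% loss, 35 / 0.85 = 41.2, so 42 per arm. Both stated figures are reproduced, and they belong to an unadjusted comparison of changes. By the noncentral t distribution, power at 35 per arm is 0.80 one-sided and 0.70 two-sided.

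**2. Formulas.** Let s0 and s1 be the baseline and follow-up SDs within an arm and r their correlation.
- Change score: variance = s0² + s1² − 2·r·s0·s1.
- Baseline-adjusted model (ANCOVA): residual variance = s1²(1 − r²).
- The first minus the second is (s0 − r·s1)². This is never negative, and it is zero only when the true slope r·s1/s0 equals 1.

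Apart from one degree of freedom and a small-sample term, adjustment therefore cannot be worse.

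**3. Inputs that the article does not give.** These are assumptions.
- SD 5 is taken as the SD of change, as the reproduction in step 1 implies.
- Baseline SD: eligibility requires at least 15 headache days a month, about 7 to 14 on a two-week diary, and the pilot baseline mean was 11. The largest SD on 7 to 14 with mean 11 is √((14 − 11)(11 − 7)) = √12 = 3.46. The range used is 2 to 3.46.
- Correlation: 0.2 to 0.7.

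Setting the change variance to 25 gives s1 = r·s0 + √(25 − s0²(1 − r²)).

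**4. Results at 35 per arm, difference 3 days** (noncentral t, 67 degrees of freedom for ANCOVA):

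| s0 | r | s1 | ANCOVA / change variance | Power, one-sided | Power, two-sided |
|---|---|---|---|---|---|
| 2 | 0.2 | 5.00 | 0.960 | 0.814 | 0.714 |
| 2 | 0.5 | 5.69 | 0.971 | 0.809 | 0.709 |
| 2 | 0.7 | 6.19 | 0.782 | 0.878 | 0.799 |
| 3 | 0.2 | 4.64 | 0.828 | 0.861 | 0.776 |
| 3 | 0.5 | 5.77 | 0.999 | 0.800 | 0.697 |
| 3 | 0.7 | 6.62 | 0.893 | 0.837 | 0.745 |
| 3.46 | 0.2 | 4.36 | 0.731 | 0.896 | 0.824 |
| 3.46 | 0.5 | 5.73 | 0.986 | 0.804 | 0.703 |
| 3.46 | 0.7 | 6.77 | 0.935 | 0.822 | 0.725 |

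The largest gain, at 0.731, needs every patient to have either 7 or 14 baseline days. The rows with r = 0.7 need follow-up SDs of 6.2 to 6.8, close to the largest SD that a 0 to 14 diary allows (√(7 × 7) = 7). The ends of the range are therefore less plausible than the middle, where the gain is small.

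**5. Chance imbalance, as an illustration.** Take s0 = 3 and r = 0.3. Then s1 = 0.9 + √(25 − 9 × 0.91) = 5.0, and the slope is 0.3 × 5 / 3 = 0.5. One standard error of baseline imbalance is 3 × √(2/35) = 0.72 days. The change-score estimate then differs from the adjusted one by (1 − 0.5) × 0.72 = 0.36 days, against a target of 3 days.

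**6. Doses.** The same algebra applies, but the article gives neither a baseline SD nor a correlation, so no range is worked out.

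**The case against.** The strongest defence is that the plan is consistent with itself. It is sized on a difference in reduction and tests that same difference, its figures reproduce, and the test is unbiased over randomisations. All of this stands. The matter is efficiency and conditional accuracy, not validity, and the planned power is not missed.

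Four stronger readings are tempting, and the document does not support them.

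- *A large loss of power.* If baseline and follow-up SDs were equal, two-sided power would rise from 0.70 to 0.87, 0.82 and 0.77 at r = 0.3, 0.5 and 0.7. With a change SD of 5, that needs a baseline SD of 5/√(2(1 − r)) = 4.2, 5.0 and 6.5 days. All exceed the 3.46 that eligibility suggests. Some fortnights may hold fewer than 7 headache days, but even the full 0 to 14 range with mean 11 allows no more than √(11 × 3) = 5.74.
- *An underpowered trial.* The two-sided figure of 0.70 comes from the one-sided significance level, which is a separate matter.
- *An analysis of completers only.* A patient without a follow-up diary has no change score, and the Sample size section allows for this: "With a calculated loss of participants in the full trial of 15" per cent. Yet the article says "The statistical analysis will be performed according to the intention-to-treat principle" and nowhere limits the analysis to patients with follow-up. How missing diaries are handled may properly be set out in the full protocol or analysis plan. A figure for bias from such losses would need inputs that the article does not give.
- *Covariates picked after seeing imbalance.* The regression sentence gives no selection rule, so this cannot be read into it. The planned regression also answers part of the worry about imbalance, though only as a supporting result.

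**Conclusion.** The point holds as a low-cost improvement. The article makes an unadjusted change-score test its main comparison while a baseline value of each primary outcome is on file. Adjustment is never less precise in large samples. Under the stated assumptions for headache days (change SD 5, baseline SD 2 to 3.46, r 0.2 to 0.7), it reduces the variance by between 0% and 27%. The benefit may thus be negligible, and it cannot be settled without the pilot correlation. The firmer reason to change is that a pre-specified covariate protects the primary estimate from chance baseline imbalance in a small trial.

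**What to change.** State that the primary estimate is the between-group difference in headache days at follow-up from a linear model with treatment and the patient's own baseline headache days as a pre-specified covariate. Do the same for medication doses.

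Preferably fit this as a repeated-measures model over 8 and 26 weeks, with treatment and baseline effects allowed to differ by visit, and say which visit gives the primary estimate. Patients with either follow-up diary then contribute. Baseline adjustment alone does not bring in patients without an outcome, and those with neither follow-up diary still need a stated assumption.

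Keep the change-score t-test, or the non-parametric test, as a supporting check. The latter remains useful because day counts are bounded and dose counts may be skewed.

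The cost is a change of wording and one degree of freedom in the single-visit model, with no extra patients, visits or measurements. The stated 35 and 42 per arm can stand.

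### The observed distribution decides whether the primary p-value tests the mean difference the trial is sized on, and whether an effect size is reported

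*Protocol article*

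**What the plan says.** Under Statistical analysis, the article states that for each patient "the change between baseline and follow-up will be calculated for all primary and secondary outcome measures". It continues: "Between group differences and 95% confidence intervals will be calculated, and tested using the Student t-test in case of normal distributions". The next sentence gives the alternative: "Non paramaratric testing will be used for non-normal distributions". A later paragraph adds a second condition: "If results on primary outcomes show normal distributions we will compute effect sizes (standardised mean differences" and grades the result as small, medium or large. No substitute is given for the non-normal case.

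The rule covers both primary outcomes, which the Primary outcome measures section lists as "1) the frequency of days with headache, and 2) use of pain medication (no. of doses NSAIDs or simple analgesics". Both come from a two-week diary and are assessed at 8 and 26 weeks.

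The Sample size section works in means throughout: "we aim to detect a difference in reduction of at least 3 days (SD 5) between both groups". For medication use it gives a detectable difference of 0.5 doses with SD 0.8.

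**The concern.** A t-test on change scores addresses a difference in means. A rank test addresses a shift in distribution, or the probability that a patient in one arm does better than a patient in the other. Under this rule the data decide which of these questions the primary p-value answers, while the trial is sized for only one of them.

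If the switch fires, three things follow. The p-value no longer tests the 3-day or 0.5-dose mean difference. If the mean difference and its confidence interval are still reported, they may not agree with that p-value. The standardised effect size is dropped. The same outcome could also be tested in different ways at 8 and at 26 weeks, which makes the two results harder to compare.

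The switch is a realistic path. A two-week diary bounds headache days at 0 to 14. The pilot mean was 11 at baseline, and after 8 weeks it was 7 in the GP group and 3 in the manual therapy group, the last being close to the floor. Medication use is a low count: "The participants in the pilot study reported taking on average 2 doses of NSAID or analgesics per 2 weeks".

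**Working it through.** **1. The plan's own figures, which reproduce.** The Sample size section states: "To detect this difference with a one-sided significance level of 0.05, and power of 0.80 we have to include at least 35 patients" per group.

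- Formula: n per group = 2 × (z for 0.95 + z for 0.80)² × (SD / difference)².
- Headache days: 2 × (1.645 + 0.842)² × (5/3)² = 2 × 6.18 × 2.78 = 34.4, so 35. Power at 35 per group is 0.807 by the normal approximation and 0.800 by the exact t distribution.
- Doses: 2 × 6.18 × (0.8/0.5)² = 31.7, so 32. Power at 35 per group is 0.834.
- Loss of 15%: 35 / 0.85 = 41.2, so 42 per group, as stated.

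No figure is disputed. The calculation shows that the sizing quantity is a difference in means. In standardised units it is 3/5 = 0.6 for days and 0.5/0.8 = 0.625 for doses, both medium on the plan's own scale. This is the effect size that the plan would leave out for non-normal results.

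**2. How often the switch might fire.** The article gives no distribution, trigger or named rank test, so all of these are assumptions:

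- 35 patients per arm and 4,000 runs per scenario.
- Trigger: Shapiro-Wilk p < 0.05 in either arm, applied to change scores.
- Fallback: Mann-Whitney test. All tests two-sided at 0.05.
- Headache days: beta-binomial on 0-14 with baseline mean 11, baseline and follow-up drawn independently. Follow-up means are 7 and 4 (the planned 3-day difference), or 7 in both arms (no effect).
- Doses: negative binomial with mean 2, against a follow-up mean of 2 or 1. The SD of change is about 3.9, much wider than the plan's 0.8.

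| Change scores | Switch fires | Two-stage rule significant | t-test and rank test disagree |
|---|---|---|---|
| Normal, SD 5, no effect | 9.8% | 5.0% | 1.7% |
| Normal, SD 5, 3-day effect | 9.5% | 69.1% | 6.4% |
| Days, SD 4.9, no effect | 17.0% | 5.1% | 1.4% |
| Days, SD 4.9 and 4.6, 3-day effect | 49.7% | 72.8% | 4.8% |
| Days, SD 5.6, no effect | 36.5% | 4.5% | 1.0% |
| Days, SD 5.6 and 5.1, 3-day effect | 77.0% | 62.6% | 4.6% |
| Doses, SD 3.9, no effect | 88.4% | 5.2% | 3.3% |
| Doses, follow-up mean 2 against 1 | 93.3% | 20.3% | 9.6% |

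A variant with baseline days restricted to at least 7 and an SD of change of about 4.9 gave 71% under the planned effect. A further set of assumed diaries brought the lower end to about 40%. For headache days the range is therefore about 40-77% under the planned effect and 17-37% under no effect. Truly normal data would give about 10%. The dose rows show only what strong skewness would do, and their spread is not the plan's.

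**3. Error rate.** Across the no-effect rows the two-stage rule rejects in 4.5-5.2% of trials.

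**4. The alternative.** In a separate check with assumed 0-14 diaries (35 per arm, two-sided 0.05), a baseline-adjusted mean difference had power of 0.86-0.87, against 0.78-0.86 for the two-stage rule. Type I error of the two-stage rule was 0.050-0.052 there.

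**The case against.** Several points on the other side are sound.

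- **Alpha.** A reader might infer that choosing the test after seeing the data spends more than the nominal 5%. The simulations do not show this. The rule is also stated in advance, and the Blinding section has an independent statistician audit and verify the analysis. That inference should not be drawn.
- **Confidence interval.** A reader might infer that the mean difference and its interval disappear when the test switches. The sentence can equally be read as giving both in every case, with only the test depending on normality. On that reading, what remains is a possible mismatch between interval and p-value.
- **Baseline adjustment.** A rank test on change scores is no less adjusted than a t-test on change scores. The switch loses nothing here, and the section separately plans a regression on baseline characteristics.
- **Size of the switch rate.** It rests on an assumed trigger and assumed distributions, and no single percentage can be defended.
- **Effect size.** Limiting a standardised mean difference to normal data is a common convention, and the measure is supplementary.
- **Detail left elsewhere.** A condensed article may leave the normality criterion and the name of the rank test to a fuller document. Their absence is not held against the plan.

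None of this removes the core. The article itself states a rule under which the primary test, and with it the quantity tested, depends on the observed outcomes, while the sample size fixes that quantity as a mean difference.

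**Conclusion.** The point holds as a badly fixed rule, not as missing detail. If the fallback is used, the primary p-value does not test the 3-day or 0.5-dose mean difference, may not match the reported interval, and comes without the standardised effect size. For headache days the fallback is plausible: about 40-77% of simulated trials under the planned effect and 17-37% under none, given the assumed bounded counts and the assumed Shapiro-Wilk trigger.

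The practical consequence is moderate. The two tests disagreed on significance in about 1-10% of simulated trials, and type I error stayed at about 5%. The documents support a concern about an unfixed estimand and estimate. They do not support a claim of inflated alpha, or that the confidence interval is certainly lost.

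**What to change.** For each primary outcome, name one analysis that applies whatever the distribution: the between-group mean difference at follow-up, adjusted for the baseline value (ANCOVA), with a robust or bootstrap 95% confidence interval. Use it at both 8 and 26 weeks. Always report that difference, its interval and the standardised effect size.

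Keep the rank test as a sensitivity analysis. Treat any count model for doses in the same way: a rate ratio as the main result would replace the sized mean difference with another estimand, which is the fault being corrected.

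This changes only the analysis wording. The baseline diary is already collected, and no patients, visits or measurements are added. The wording should be settled before outcome data are examined by arm.
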